## Main and Secondary Hypothesis

We hypothesize that minimally invasive approaches—both laparoscopic and robotic—will lead to better early postoperative outcomes compared with open repair in patients with inguinoscrotal hernias. Specifically, we expect lower rates of surgical site infections and overall complications (as graded by the Clavien–Dindo classification), reduced postoperative pain as measured by the Visual Analogue Scale, and shorter hospital stays.

We also hypothesize that these advantages will translate into an improved early health-related quality of life, as assessed through the EQ-5D-5L questionnaire.

Regarding long-term results, we hypothesize that minimally invasive repair may be associated with lower rates of chronic pain and better long-term quality of life compared with open surgery.

Additionally, we expect that recurrence rates at 2 years will not significantly differ between minimally invasive and open approaches, reflecting comparable long-term durability of the repair.

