### Sample Size Calculation and Justification

The sample size was calculated to detect clinically significant differences in postoperative outcomes between minimally invasive (laparoscopic or robotic) and open approaches for inguinoscrotal hernias. Specifically, the calculation was based on the hypothesis that minimally invasive approaches would decrease postoperative complication rates by 20% compared with open surgery and lead to a 2-point reduction in postoperative pain (measured using the Visual Analog Scale).

Assuming a 5% significance level (two-sided α) and 80% power (1−β), and accounting for an estimated 5% loss to follow-up, a total of 150 patients (50 per surgical group: open, laparoscopic, robotic) will be required. This sample will enable the detection of statistically and clinically meaningful differences across the three groups using analysis of vairance (ANOVA) or Chi-square tests as appropriate.

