### Outcome Measures

Primary outcomes:The primary outcomes of this study encompass the postoperative outcomes.-Surgical site infection and surgical site occurrence will be analyzed, and general complication will be assessed and graded using the Clavien–Dindo classification system.Surgical site occurrence (SSO) was defined as any wound-related complication within 30 days after surgery, including both infectious and non-infectious events. SSO included seroma, hematoma, wound dehiscence, and SSI.Surgical site infections (SSI) were assessed within 30 days after surgery. SSI were classified as superficial, deep, or organ/space infections. Superficial SSI involved the skin and subcutaneous tissue, while deep SSI involved the fascia or muscle layers. Organ/space SSI referred to infections involving anatomical structures manipulated during surgery other than the incision.-Postoperative pain will be evaluated using the VAS.-The length of hospital stay will be recorded for all patients as a key marker of recovery.-Furthermore, the assessment of health-related QoL using the QoL questionnaires EuroQol EQ-5D-5LTM will continue.-Return to normal daily activitiesSecondary outcomes:The secondary endpoints will focus on long-term outcomes.-Evaluation of hernia recurrence-Chronic pain and health-related QoL will be assessed at long-term follow-up intervals.

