#### Postoperative Data

Surgical site eventsPostoperative adverse events (all occurrences other than surgical site occurrences, including ileus, pulmonary embolism, or pneumonia) according to the Clavien–Dindo Classification up to 30 daysDuration of analgesic medication useHospital readmission rateSick leave duration, defined as the number of days until return to work or to normal daily activitiesRecurrence rate, both clinically and radiologically (via ultrasonography or computed tomography), will be evaluated at 6 months, 1 year, and 2 years.QoL using the EuroQol EQ-5D-5LTM Spanish version: patients will receive questionnaires at inclusion and at 1, 6, 12, and 24 months postoperatively by mail, digitally, or in person according to their preference. Using the EQ-5DTM questionnaire, all participants will be asked to score the following five aspects of health status: mobility, self-care, usual activities, pain/complaints, and mood (anxiety/depression). This questionnaire is considered the most representative QoL tool for cost-effectiveness–related studies [14].Pain intensity using the VASReturn to normal daily activities

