### Statistical Analyses

Statistical analysis will follow the intention-to-treat principle. Descriptive statistics will be employed for summarizing baseline characteristics and perioperative outcomes across the three surgical groups: open, laparoscopic, and robotic.

Univariate analyses (Chi-square or Fisher’s exact test and ANOVA or Kruskal–Wallis test for categorical and continuous variables, respectively) will be performed for comparing outcomes, including complication rates, recurrence, surgical site infections, and hospital length of stay.

To control for potential confounders, multivariate logistic regression models will be applied, particularly for primary outcomes, including postoperative complications (classified using the Clavien–Dindo classification system and Comprehensive Complication Index), hernia recurrence, and chronic postoperative pain.

Time-to-event outcomes (e.g., time to recurrence) will be analyzed using Kaplan–Meier survival curves and compared using log-rank tests. To assess predictors of recurrence or reoperations, Cox proportional hazards models will be employed.

Subgroup analyses will be considered on the basis of patient age, BMI, hernia type (primary vs. recurrent), and surgical approach. P < 0.05 will be considered statistically significant.

To assess data quality, protocol adherence, and recruitment balance across centers, an interim descriptive analysis may be performed following the inclusion of 50% of the expected patient sample.

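### Seven co-equal primary outcomes with none ranked first, recurrence and chronic pain labelled both secondary and primary, and an unclear set of complications behind the sample size

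*Protocol article*

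**What the plan says.** **Primary and secondary labels.** Outcome Measures names seven primary outcomes without ranking them: surgical site infection (SSI), surgical site occurrence (SSO), general complications graded by Clavien–Dindo, VAS pain, length of stay, EQ-5D-5L, and return to daily activities. It continues: "The secondary endpoints will focus on long-term outcomes", and lists recurrence, chronic pain and long-term quality of life there. Statistical Analyses applies multivariable models "particularly for primary outcomes, including postoperative complications (classified using the Clavien–Dindo classification system and Comprehensive Complication Index), hernia recurrence, and chronic postoperative pain". That sentence moves recurrence and chronic pain to primary. It also brings in the Comprehensive Complication Index, which Outcome Measures does not list.

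**Criterion.** The one statement on significance in the analysis section is "P < 0.05 will be considered statistically significant".

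**Which complications.** Main and Secondary Hypothesis speaks of "overall complications (as graded by the Clavien–Dindo classification". Postoperative Data lists surgical site events separately and applies Clavien–Dindo to adverse events defined as "all occurrences other than surgical site occurrences, including ileus, pulmonary embolism, or pneumonia". Sample Size Calculation and Justification assumes that minimally invasive surgery "would decrease postoperative complication rates by 20% compared with open surgery" and will "lead to a 2-point reduction in postoperative pain". It does not say which complications are counted or at which visit pain is measured.

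**The concern.** A reader cannot tell which result decides the study. On the Outcome Measures list, the main result falls largely in the short-term publication. On the Statistical Analyses list, part of it waits for the two-year publication. One of the outcomes called primary there, recurrence, is also one where the hypothesis section expects no significant difference at two years.

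With seven primaries of equal rank and one blanket threshold, a positive finding on any of them could be presented as the study's main result. The sample size cites only complications and pain, so the other listed primaries have no stated power basis. For complications, the quantity that was powered cannot be identified with certainty, because three sections describe the set of events differently.

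**Working it through.** **Step 1. The labels side by side.**

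| Outcome | Outcome Measures | Statistical Analyses |
|---|---|---|
| SSI, SSO, VAS, stay, EQ-5D-5L, return to activities | primary | not named in the sentence on primary outcomes |
| Clavien–Dindo complications | primary | primary |
| Comprehensive Complication Index | not listed | used to classify a primary outcome |
| Recurrence | secondary | primary |
| Chronic pain | secondary | primary |

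The first list has seven primaries. Adding recurrence and chronic pain gives nine. Once the label clash is corrected, seven remain, so seven is the count to use.

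**Step 2. The plan's own figure.** The inputs are "Assuming a 5% significance level (two-sided α) and 80% power (1−β), and accounting for an estimated 5% loss to follow-up", with 50 per group. The open-group complication rate and the VAS standard deviation are not given, so 50 cannot be reproduced from stated inputs. It can only be matched under assumptions.

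- Two proportions, pooled, per group: n = [1.960·√(2p̄(1−p̄)) + 0.842·√(p₁(1−p₁)+p₂(1−p₂))]² / (p₁−p₂)². If the 20% is an absolute drop, 24% vs 4% gives 47, and 47/0.95 rounds up to 50. 25% vs 5% gives 49, and 49/0.95 rounds up to 52.
- Two means, per group: n = 2·(1.960+0.842)²·SD²/2². An SD of 3.45 gives 47, which becomes 50 after 5% loss.
- If the open rate were higher with the same absolute drop, the need after 5% loss rises: 66 for 30% vs 10%, 87 for 40% vs 20%, and 98 for 50% vs 30%.
- If the 20% is a relative drop, the need before loss runs from 1,447 per group (open rate 20%) to 270 (open rate 60%).

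The stated size therefore does not reveal which set of complications was meant. The required size also depends strongly on the open-group rate, and that rate depends on whether wound events are counted.

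**Step 3. Chance of at least one false-positive primary.** This assumes no true difference on any outcome and one two-sided test at 0.05 per outcome.

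- Independent outcomes: 1 − 0.95⁷ = 0.302, and 1 − 0.95⁹ = 0.370.
- Correlated outcomes: simulated test statistics Zⱼ = √ρ·C + √(1−ρ)·Eⱼ with C and Eⱼ standard normal, 400,000 draws, counting how often the largest |Zⱼ| exceeds 1.96.

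| Assumed common correlation | 7 primaries | 9 primaries |
|---|---|---|
| 0 | 30% | 37% |
| 0.3 | 27% | 33% |
| 0.5 | 23% | 27% |
| 0.7 | 18% | 20% |

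The documents give no correlations, so 0.3 to 0.7 is an assumed range. Independence does not hold here, because the protocol defines SSO to include SSI.

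**Step 4. Choices not counted above.** Table 1 schedules VAS at day 1, day 7, day 30, 6 months, 1 year and 2 years, and no visit is named as primary. Since long-term pain is listed as secondary, the three early visits are the plausible candidates. Three surgical groups also allow more than one comparison per outcome.

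**Step 5. Cost of the alternative, splitting alpha.** Bonferroni over seven gives 0.05/7 = 0.0071. For an assumed 25% vs 5%, the size per group after 5% loss rises from 52 to 84. Naming one primary outcome avoids this.

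**The case against.** **Multiplicity may be left to an analysis plan.** This is a non-randomised cohort, a hierarchy of outcomes is often set out in a statistical analysis plan, and the 0.05 threshold does not say that no adjustment will be made. A reader might infer that the protocol rules adjustment out; it does not say so. What stands is that the protocol itself gives two answers on what is primary and gives seven outcomes equal rank. A separate plan would not remove the contradiction in labels.

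**The error rate could be overstated.** A reader might take 37%, or even 30%, as the actual risk. The 37% counts the union of two conflicting lists, and both figures assume independence, which the nesting of SSI in SSO contradicts. The correlated range for seven outcomes is the fair statement. Likewise, not all six postoperative VAS visits are plausible primaries.

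**Wound events.** A reader might infer that the protocol both includes and excludes wound events in the graded outcome, or that such events would be lost. The documents do not support that. Outcome Measures and Postoperative Data consistently separate surgical site events from other graded complications, and SSI and SSO are primary outcomes in their own right. Inclusion rests on the one word for overall complications in the hypothesis section. Nor does any section say that the powered rate leaves wound events out, or rank them as the outcome expected to differ most. What stands is an ambiguity about which set the sample size refers to.

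**Model form.** A reader might infer that logistic regression is wrong for an ordered grade or a score. The protocol does not restrict it to a binary model, and an ordinal model or a dichotomised grade would both fit its wording. This is no finding.

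**Conclusion.** The point holds for three things. First, recurrence and chronic pain are secondary in one section and primary in another; this is a plain contradiction and rests on no assumption. Second, seven primaries of equal rank with P below 0.05 as the only stated criterion leave the deciding outcome undefined. The resulting chance of at least one false-positive primary is about 18% to 27%, roughly four to five times the nominal 5%, under assumed common correlations of 0.7 to 0.3 and no true differences. It is 30% in the independent case. Third, the complications behind the sample size are not identified; this is an ambiguity to clarify, not a proven omission of wound events.

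**What to change.** - In Statistical Analyses, label recurrence and chronic pain secondary, in line with Outcome Measures.
- Name one primary outcome from the two that the sample size cites, for example any complication within 30 days. State in the hypothesis, sample size, Outcome Measures and Postoperative Data sections whether SSO and SSI count. If they do, grade them by Clavien–Dindo as well and check the complication rate assumed in the sample size.
- Make VAS at one named early visit the key secondary outcome, tested only if the primary succeeds.
- Report the remaining outcomes as secondary, with 95% confidence intervals.

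The cost is wording in five sections and, if wound events are counted, a grading field for them in the eCRF. Naming one primary needs no alpha split across outcomes and in itself no extra patients. If wound events are added, however, the assumed rate and hence the sample size may need another look. The downside is that fewer outcomes can be called confirmatory, and pain can be tested only after a positive primary result. The choice should be made before outcomes are compared between groups.

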**Methods and analysis:**

This national multicenter prospective observational cohort study will include patients undergoing elective or urgent repair of European Hernia Society-classified inguinoscrotal hernias (S1–S3) using open, laparoscopic, or robotic techniques. Adults (>18 years) from various hospitals in Madrid will be recruited. Data on patient demographics, intraoperative variables, postoperative complications, postoperative pain (Visual Analog Scale score), quality of life, and hernia recurrence over a 2-year follow-up will be collected. A minimum of 100 patients (50 per group) is required for detecting statistically significant differences, assuming 5% loss to follow-up.

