### Duration and Schedule

#### Phase 1: Patient Inclusion

The recruitment period for patient inclusion in the clinical trial will span 22 months. As the variable “recurrence” requires a maximum follow-up of 2 years postoperatively, this study will conclude at 24 months following the inclusion of the last patient. Therefore, the total study duration, from the inclusion of the first patient to the collection of data from the last patient, will be 46 months.

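### Multivariable logistic and Cox models are planned for recurrence with no event rate behind them; at assumed rates of 2% to 5%, about 3 to 7 events would have to carry them

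*Protocol article*

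**What the plan says.** The Statistical Analyses section of the protocol article gives recurrence two regression models.

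- **Logistic.** "To control for potential confounders, multivariate logistic regression models will be applied, particularly for primary outcomes". The outcomes then listed include hernia recurrence, although Outcome Measures places recurrence among the secondary outcomes. Reoperation is not in this list.
- **Cox.** "To assess predictors of recurrence or reoperations, Cox proportional hazards models will be employed". Kaplan–Meier curves and log-rank tests are planned alongside.

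The same section describes three groups: open, laparoscopic and robotic. It also provides for Fisher's exact test in the unadjusted comparisons. It names no covariates.

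The size comes from Sample Size Calculation and Justification: "accounting for an estimated 5% loss to follow-up, a total of 150 patients", in three groups of 50. It rests on a reduction in complications and on a difference in VAS pain. Follow-up is fixed under Phase 1: Patient Inclusion: "this study will conclude at 24 months following the inclusion of the last patient". The hypotheses expect no significant difference in 2-year recurrence between minimally invasive and open repair. No recurrence or reoperation rate is stated anywhere in the article.

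**The concern.** A regression model for a binary or time-to-event outcome draws its information from the events, not from the number of patients. If an approach, or a level of a covariate, has no recurrences, maximum likelihood drives its log odds ratio or log hazard ratio to minus or plus infinity. Short of that, with very few events per term, the estimates are unstable and tend to be too extreme.

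The article commits to these estimators without showing that the events can support them. The results would go into the planned two-year publication, and the Discussion hopes to guide future guideline recommendations. An implausibly large or undefined ratio reported there as a predictor of recurrence could mislead.

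**Working it through.** **The plan's own size.** 3 × 50 = 150, and 150 × 0.95 = 142.5, so about 142 evaluable patients, or about 47 per approach. The 50 per group cannot be reproduced, because neither the baseline complication rate nor the VAS standard deviation is given. For example, 24% versus 4% needs 47 per group, and 47 / 0.95 rounds up to 50, but that pair of rates is only one that fits. Recurrence plays no part in the calculation.

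**Assumption.** The 2-year recurrence rate p is taken as 2%, 3%, 5% or 10%, equal in all groups, in line with the stated expectation of no significant difference.

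**Formulas.**

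- Expected events = 142 × p.
- P(at least one of three approaches has no event) = 1 − (1 − (1 − p)^47)^3.
- P(an empty group, pooled minimally invasive versus open) = 1 − (1 − (1 − p)^47)(1 − (1 − p)^95).

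Example at 2%: 0.98^47 = 0.387 and 0.98^95 = 0.147. Three approaches: 1 − 0.613^3 = 0.77. Pooled: 1 − 0.613 × 0.853 = 0.48.

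| Assumed 2-year rate | Expected events | An approach with none (three groups) | Empty group (pooled contrast) |
|---|---|---|---|
| 2% | 2.8 | 77% | 48% |
| 3% | 4.3 | 56% | 28% |
| 5% | 7.1 | 25% | 10% |
| 10% | 14.2 | 2% | 1% |

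For three groups, the chance of an empty approach is 50% at a rate of about 3.3%, 20% at about 5.4% and 5% at about 8.3%.

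**Events per model term.** Two approach terms plus one term for each of the seven listed baseline characteristics (age, sex, BMI, ASA, Charlson, hernia type, hernia classification) make nine. That set is illustrative, since the article does not say which enter the model. Nine terms outnumber the expected events whenever p is below 9 / 142 = 6.3%. At 10% there are 14.2 / 9 = 1.6 events per term.

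**Illustrative simulations of the logistic model.** With two approach terms, seven baseline terms and no true effects, 95%, 88%, 68% and 29% of data sets gave no finite or converged fit at rates of 2%, 3%, 5% and 10%. A separate simulation with two approach terms and six covariate parameters, checking directly for separation, found some non-finite coefficient in 96%, 89%, 62% and 22%. Covariate prevalences were assumed. The failing coefficient could be any one in the model, not only an approach. No Cox model was simulated and nothing was computed for reoperation.

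**If the abstract's size applies.** The abstract gives a different total: "A minimum of 100 patients (50 per group) is required for detecting statistically significant differences, assuming 5% loss to follow-up". That leaves 100 × 0.95 = 95 patients, and 1.9, 2.9, 4.8 and 9.5 expected events at the same four rates.

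**The case against.** The strongest reply is that the article states no event rate, so few events cannot be presented as a fact. That stands. Recurrence is sought both clinically and by imaging, and S1 to S3 hernias and urgent cases are admitted, so a higher rate is possible. A reader might infer that the models will usually have no finite estimate for an approach. That holds at about 3% or below, is a minority risk at 5%, and does not hold at 8% to 10%. For the pooled contrast, which is the study's stated objective, the risk is lower throughout.

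Other readings also go beyond the text:

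- Logistic regression is listed for recurrence, not for reoperation.
- The Cox models are not called multivariable. Fitting predictors one at a time would fit the wording and would ease the problem of too many terms, though not that of an empty group.
- No Wald test is specified, and score or likelihood-ratio tests cope with an empty group.
- A logistic model for 2-year recurrence does ignore censoring, but with 24 months planned for everyone and 5% expected loss, this is minor.

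Fisher's exact test, Kaplan–Meier and log-rank tests are already planned and remain usable with few events. Covariate selection and sparse-data methods may also sit in an analysis plan that is not shown, so their absence is not an error in itself.

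What remains is that the article itself names the regression models for recurrence and offers nothing to show that the events can carry them. Even 14 events are too few for two approach terms plus several confounders.

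**Conclusion.** The point holds in a conditional form. If 2-year recurrence is 2% to 5%, about 3 to 7 events are expected among about 142 patients. The chance that at least one approach has none then runs from 77% down to 25%, and for the pooled contrast from 48% down to 10%. Ordinary maximum-likelihood multivariable models would then often give non-finite or unstable ratios, for the approach or for a covariate. At 10% an empty approach is improbable, but the model would still be overloaded.

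This rests on the total of 150, the 5% loss, equal rates across groups and an assumed recurrence rate. The documents do not support the stronger claim that the models will certainly fail, or that the approach estimate is always the one affected. Because recurrence is a secondary outcome and the remedy is a change of wording, this is a cheap improvement rather than a flaw that threatens the main comparison.

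**What to change.** In the Statistical Analyses section:

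1. Take recurrence out of the logistic regression list and analyse it by time-to-event methods only. Report the Kaplan–Meier 2-year cumulative incidence by approach with a 95% confidence interval, using an interval method that still works when an approach has no events.
2. Fit the Cox model for recurrence or reoperation with Firth penalization and profile-likelihood intervals, with pooled minimally invasive versus open as the main contrast.
3. Cap the number of adjustment terms by the observed events, for example one pre-treatment summary score when events are few.
4. Keep the aim of studying predictors, but label those results exploratory, or report them descriptively, when events are too few.

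The change needs no extra patients or data. It costs some adjusted predictor ratios, and estimates are shrunk toward no effect, possibly noticeably when there are very few events. Penalization also cannot help if there are no recurrences at all, which at a 2% rate has a probability of 0.98^142, about 6%; only the cumulative incidence and its interval could then be reported.
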